## Abstract

**Background:** The access to digital tools for parents is increasing, and further exploration is needed to gain knowledge about parents' experiences in using such tools, for example, when preparing for childbirth and parenthood. This study protocol describes a prospective study that will explore serious games as digital tools for parental support, and both parents' and healthcare professionals' views will be included. The objectives of the prospective study are to explore two different serious games: (1) Childbirth Journey (Swedish: Förlossningsresan), relating to pregnancy, childbirth and parenthood; and (2) Interplay (Swedish: Samspel), relating to parental couple relationships and parenthood.

**Methods:** An intervention study will be conducted. The study will include four different sub-studies (A–D) with both qualitative and quantitative methods and a longitudinal design. Both parents (A, B and D) and healthcare professionals (C) will be included, and data will be collected through interviews (A–C) and repeated web-based questionnaires (D). Data will be analysed using phenomenography and qualitative content analysis (A–C), and descriptive and analytical analyses will be performed for comparisons and associations (D).

**Discussion:** The value of monitoring and reporting on developments and trends in digital innovation for public health has been stipulated by the World Health Organization. The prospective study will contribute further knowledge about multidisciplinary development of digital tools as professional support for parents, as well as knowledge about parents' and healthcare professionals' experiences using digital tools concerning pregnancy, labour, parenthood and parental couple relationships.

**Trial Registration:** This study was retrospectively registered (02/10/2020) within the ISRCTN with ID: ISRCTN18017741. http://www.isrctn.com/ISRCTN18017741.

## Background

Expectant and new parents turn to digital sources, such as the Internet, to obtain information about pregnancy, labor, and parenthood (1–3), but they sometimes find it difficult to evaluate the trustworthiness of the information (4–6). Furthermore, the development of digital technology in society is rapid (7), and digital tools available for parents are, sometimes, unexplored. For example, in Denmark, a serious game was developed by Region Midt/Hospitalsenheden West, Denmark (Danish title: *Samspil*), with the intention of strengthening new parents' couple relationships and cooperation within parenthood. Since 2019, *Samspil* has been offered to new parents in Denmark, and an evaluation has shown that both parents and professionals express interest in using it (8). However, there is a lack of research on parents' and professionals' experiences using *Samspil* or other serious games as digital tools regarding childbearing. This study protocol describes a prospective study that will provide additional perspectives on how parents' couple relationships and parenting can be supported with digital tools.

Expectant parents experience one of the most drastic life changes for the human being—the transition to parenthood, and they pose, usually, issues on both medical and practical matters (9). In recent years, it has become increasingly common for expectant parents to turn to digital sources for health information (1, 2). Overall, there has been rapid development of advanced technology in society, and research shows that humans are experiencing that the rapid integration of digital technology affects both their personal and professional lives (7). Nevertheless, expectant parents search for health-related information online, and the Internet plays an important role in providing them with support (3). One literature review revealed that most expectant mothers have access to the Internet, and they use it to retrieve information about pregnancy, childbirth, and the expected child (10). In addition, expectant fathers have been shown to obtain Internet-delivered information related to parenting, how to support their pregnant partner, and how to promote theirs and their family's well-being and health (11). Both expectant mothers and fathers also use the Internet to read about others' experiences of giving birth to a child and becoming a parent (12, 13). Previous research shows that parents want information on the Internet to be immediate, regular, detailed, and entertaining. Also, they prefer information provided by health care professionals and information that is practical and reassures their knowledge (1). In a recent study, Bäckström et al. (14) showed that parents perceive that future digital parental support should provide them with opportunities to have both virtual and in-person meetings, as well as individualized support based on professional knowledge and trustworthiness. The authors claim that such future digital parental support might facilitate digital health literacy of new and would-be parents. However, further exploration is needed to gain knowledge of how digital tools should be designed so that parents could benefit from using them.

The way expectant parents seek information has been described as a “holistic learning process to seek meaning”, and it affects their decision-making process regarding pregnancy (15). For example, expectant mothers' decision-making process has been shown to involve seeking, collecting, and assessing information from healthcare professionals, other expectant mothers, and research. They base their decisions regarding pregnancy on their perceptions of safety and trustworthiness regarding the information obtained (6). Nevertheless, parents' access to digital tools is increasing (1–3, 7), and further exploration is needed to gain knowledge, for example, about parents' experiences using such tools when preparing for childbirth and parenthood.

Expectant parents are usually cared for within antenatal care. Internationally, which healthcare professionals are responsible for antenatal care varies. In Sweden and several other countries, midwives are the primary caregivers (16). However, it has been revealed that expectant parents tend to use the Internet to verify information provided by midwives within antenatal care (4, 5). Therefore, it is arguable that, instead of disregarding the use of the Internet as a source of information during pregnancy, healthcare professionals, such as midwives, should keep up to date and give expectant parents links to high-quality sites (3). The limited time for antenatal appointments with healthcare professionals can influence expectant mothers' Internet use (15), and there is a difference in how Swedish midwives refer expectant parents to information *via* the Internet (17). A reason why midwives do not refer parents to the Internet could be a lack of Internet-based sources that are deemed trustworthy or interesting to use (18). However, another reason could be a lack of Internet-based sources that are deemed trustworthy or interesting to use. Therefore, further research about digital tools for expectant and new parents is needed to gain knowledge about the content and design of digital tools to be able to promote them.

### Serious Games

Games have been a part of human culture since the dawn of civilization. The Dutch historian Huizinga even argued that games have played a central role in the development of societal structures, such as our legal system (19). Games have been used for education and training for a long time: Chess and Go have been used to teach military strategy (20), and roleplaying has been used in vocational training in many areas, including nursing education (21). The use of digital games for training started almost at the same time as the first digital games appeared in the second half of the twentieth century. Different terms have been used to describe the use of games for purposes other than pure amusement: *edugames, edutainment, learning games, games for change, educational games*, and *serious games*. In the last decade, the term *gamification* has become popular (22). The underlying principle for all of these approaches is that the motivational and recreational elements in games should be leveraged to achieve some additional goal. To a large extent, research relating to games has focussed on studies of serious games (23). In this study, we use the term *serious game* as an umbrella that covers the other approaches (i.e., edugames, edutainment, learning games, games for change, and educational games).

Two aspects that are commonly overlooked in serious games research are how to create an interesting *gaming experience* and how to *evaluate the experience* users have when playing (24). One characteristic found in most games providing gameful experiences is that they offer players challenges to overcome. Different players will have different skills and experiences, which means that it is impossible to create a game that fits all players (24). If a game is too hard, players will give up; if it is too easy, they may lose interest (25).

The focus in research studies is mainly on evaluating the effect of the game in terms of the serious goal; for example, to determine its learning or rehabilitation effect. However, Engström (26) and Martin (23) argued that there is a gap between research and the game industry. The process of game development, as it is conducted in the game industry, is not well understood. The deep interdisciplinary collaboration at game companies is rarely reflected in academia, which is organized in disciplinary structures. It becomes problematic when games are developed by researchers who lack experience in conventional game development but still approach the more difficult challenge of creating a serious game. Such approaches risk producing a game that has a good representation of the serious element but fails to give a satisfying player experience—hence, the original motivation for using games is lost. On the other end of the spectrum, there are examples of serious games that manage to give players an enjoyable experience to the extent that they forget about the context in which the game is being played. If a learner enters *gamer mode* (27), this may compromise the pedagogical goals of an exercise. An important conclusion that can be drawn from the multitude of previous studies of serious games is that they are challenging to create (28). Recent research has shown that expectant and new parents ask for more digital tools, such as serious games (14), and there is a lack of knowledge regarding serious games for expectant and new parents. Therefore, the prospective study described in this study protocol will explore serious games as digital tools for parental support, and both parents' and healthcare professionals' views will be included.

This study protocol describes a prospective study in which we will strive to tackle the challenges identified above. First, we will do this by acknowledging that they exist, which is not always done in serious games projects. Second, the research team will be composed of a mix of researchers with different backgrounds and participants with experience of game development. Within the study, two different serious games will be explored. One of them, *Childbirth Journey*, is newly developed, and no exploration of the game has previously been conducted. The other, *Interplay*, will be further developed from the original Danish version and reworked to correspond to the Swedish context. The two different serious games represent different characteristics: *Childbirth Journey* is a story-driven game focussed on conveying information facilitating expecting parents' preparation for childbirth and parenthood, while *Interplay* is a casual quiz game mostly focussed on one central message—that it is valuable to nurture one's couple relationship. Further, *Interplay* includes information about couple relationship and parenthood (this will be further described in the methods section). Subsequently, by exploring two serious games representing different characteristics and different stages of development, we will see diverse views, and thus, gain a deeper understanding about how digital tools should be provided to expectant and new parents. Both serious games will be developed in collaboration with game companies.

## Objectives

The overall aim of the prospective study is to explore two different serious games, which are as follows: (1) *Childbirth Journey* (Swedish title: *Förlossningsresan*), relating to pregnancy, childbirth and parenthood; and (2) *Interplay* (Swedish title: *Samspel*), relating to parental couple relationships and parenthood. The secondary aims of the prospective study are to explore the following:

(1) Parents' perceptions of and user behavior in *Childbirth Journey*. Research question: How do parents perceive *Childbirth Journey* as a digital parental support relating to pregnancy, childbirth and parenthood? (Study A).(2) Parents' perceptions of and user behavior in *Interplay*. Research question: How do parents perceive *Interplay* as a digital parental support relating to parental couple relationships and parenthood? (Study B).(3) Healthcare professionals' perceptions of *Childbirth Journey* and *Interplay*. Research questions: (1) How do healthcare professionals perceive *Childbirth Journey* as a digital support for parents relating to pregnancy, childbirth and parenthood, and (2) How do healthcare professionals perceive *Interplay* as a digital support for parents relating to parental couple relationships and parenthood? (Study C).(4) Parents' user behavior over time and individual sessions in *Interplay*, as well as their perceived quality of the parental couple relationship, social support, and sense of coherence related to the results in study A–C (study D).

## Methods and Design

This study protocol describes a prospective study that is explorative, and mixed methods with both inductive and deductive approaches will be used. A mixed method study, according to Creswell [(29), p. 457], “is one in which the research uses at least one quantitative method and one qualitative method to collect, analyze, and report findings in a single study”. Before designing the prospective study, a systematic literature review (submitted for review) and interviews with expecting and new parents were carried out (14) to broaden our understanding about how expecting and new parents use digital sources regarding childbearing and parenthood. The prospective study is an intervention study that includes the exploration of two different serious games, *Childbirth Journey* and *Interplay*. This prospective intervention study will include four different sub-studies (A–D), using both qualitative and quantitative methods and a longitudinal design. The qualitative studies (A–C) will be located in a county in southwest Sweden. The quantitative study (D) will be located nationally in Sweden. Participants to be included are as follows: expectant parents (A and B), new parents (D), and healthcare professionals at antenatal clinics and within family counseling (C). The different designs to be used within studies A–D are presented in Table 1. This study uses a QUAL-QUAN *sequential mixed design* according to the classification presented by Schoonenboom and Johnson (30), and it was retrospectively registered (02/10/2020) within the ISRCTN with ID: ISRCTN18017741. http://www.isrctn.com/ISRCTN18017741.

**Table 1 T1:** Overview of studies including methods, interventions, sample, data collection and data analysis.

**Study**	**Methods**	**Intervention**	**Sample**	**Data collection**	**Data analysis**
A	Qualitative method	Childbirth journey	10 parents	Interviews	Phenomenographic analysis
B	Qualitative method	Interplay	10 parents	Interviews	Phenomenographic analysis
C	Qualitative method	Childbirth journey and interplay	10-healthcare professionals	Interviews	Phenomenographic analysis
D	Quantitative method, prospective longitudinal	Interplay	120 parents	Repeated questionnaires	Descriptive and analytical analysis

### Interventions

For the interventions, two different serious games, *Childbirth Journey* and *Interplay*, are to be explored. All participants will receive one of the two serious games, depending on which part of the study they participate in. Participants in studies A and C will receive *Childbirth Journey*, and participants in studies B, C, and D will receive *Interplay*. The two different serious games are described in greater detail below.

#### Childbirth Journey

One of the serious games to be explored in this prospective study, *Childbirth Journey*, is newly developed, and no exploration of the game has previously been conducted. *Childbirth Journey* is a story-driven game. This means that the main reward from such gameplay is to experience the resulting narrative. Storytelling in games, however, poses unique challenges as it contrasts with traditional drama:

*It is a difficult balancing act between what is perhaps the biggest challenge in relation to storytelling in games: the conflict between the strong player control required for a good interactive experience and the strong author control traditionally required for good drama* (31).

The idea of serious games design is that expectant parents will be able to choose different types of scenarios for the characters to experience in the game. When expectant parents are controlling the different scenarios, they can process any concerns or fears according to their individual needs. Based on previous research on expectant parents' needs of information (1–3, 10–13), the different scenarios included deal with antenatal care; expectant parents' preparation at home; the start of labor; labor; breathing techniques and pain relief; breastfeeding and formula; postnatal care; and the postpartum period, including the first days at home with the child. *Childbirth Journey* does not pose any real obstacles to player progression. The goal of developing *Childbirth Journey* was to create a digital tool as parental support for expectant parents that could facilitate expectant parents' knowledge about preparing for childbirth and parenthood hence professional support previously has been shown to facilitate expectant parents' knowledge and understanding (32).

The content in *Childbirth Journey* is developed and controlled by healthcare professionals in antenatal, labor, postnatal, and child health care, as well as a researcher specializing in serious games, creating a multidisciplinary team. Since *Childbirth Journey* is provided digitally, this enables expectant parents in Sweden to use it without hindrance, regardless of time and space. The basis for developing *Childbirth Journey* was previous research conducted by the researchers (32), as well as interviews with expectant and new parents about their use and experiences of digital tools in relation to pregnancy, labor, and parenthood. The results of the interviews is published elsewhere (14). *Childbirth Journey* will consist of one interface for the pregnant woman and another for the partner because previous research has shown the importance of including both parental roles in professional support (32). *Childbirth Journey* will be provided both as a mobile application and as a computer version, and there will be Swedish and English versions.

In study A, expectant parents will take part in the intervention, and their experiences from and user behavior in *Childbirth Journey* will be explored. In study C, healthcare professionals will take part in the intervention, and their experiences of *Childbirth Journey* will be explored.

#### Interplay

The second serious game that will be explored for this study, *Interplay*, represents another game genre, the casual quiz game (33), where competition is a catalyst for social interaction. Many similar games contain puzzles that the player must solve to progress. These can potentially provide the player with an interesting challenge, but they may also stop a player from continuing. However, *Interplay* does not pose any real obstacles to player progression, as by focussing on the core aesthetics of the genre, we reduce the risk that some players might become stuck. *Interplay* has been used by many players in its Danish version (Danish title: *Samspil*), so the design is well tested, although it has not been explored in any research study.

In preparation for this study, the Danish version has been translated to Swedish and revised to be suitable within the Swedish context. *Interplay* includes concrete tasks and learning elements that aim to strengthen expectant and new parents' knowledge and ability to handle their role as partners and parents. The intention is that parents should use *Interplay* to help in creating a safe and well-functioning environment for them and their children. Since *Interplay* is provided digitally, this enables parents to use it without hindrance, regardless of time and space.

In study B, expectant parents and new parents will take part in the intervention, and their experiences from and user behavior in *Interplay* will be explored. In study C, healthcare professionals will take part in the intervention, and their experiences of *Interplay* will be explored. The results of study B and C will contribute with further development of the *Interplay* before conducting study D. In study D, expectant and new parents will take part in the intervention, and their user behavior over time and individual sessions in *Interplay*—as well as associated factors between parents' user behavior and experiences from *Interplay* and their perceived quality of parental couple relationships, social support, and sense of coherence—will be explored.

### Participants

In both studies A and B, parents will be recruited through midwives at antenatal units and with flyers and ads on social media. We aim to include ~10 parents in each case in studies A and B; the targeted participants for each study are described in Table 1. In study C, ~10 healthcare professionals (i.e., midwives in antenatal care, nurses in child health care, and family supporters in family counseling) will be recruited through email. The number of targeted participants in studies A–C is considered appropriate to gain trustworthy knowledge about the phenomena explored within the contextual circumstances for the research participants, hence qualitative research does not intend to generalize the results into other settings (34). Based on power calculations, ~120 parents will be included in study D. Quantitative calculation for power strength is based on an expected relationship of 0.4, which requires at least 100 participants, given power of 80% and significance level 0.05 (35). In study D, a total of 120 participant is sought to ensure power. Participants will be recruited through flyers and ads on social media. In the studies (A–D), both convenience and snowball sampling will be used. The *inclusion criteria* are as follows: (1) expectant and new parents in the study setting (A and B); (2) healthcare professionals at antenatal units and in family counseling in the study setting (C); and (3) expectant and new parents in Sweden (D). Inclusion in the study is regardless of whether the pregnancy or birth is high or low risk, or if the baby is born premature or with illness, which means that parents are included on equal terms as expecting or new parents. The *exclusion criteria* are as follows: (1) parents with insufficient ability in speaking, reading, or understanding Swedish (B and D) or English (A); (2) parents or healthcare professionals who do not have access to mobile phones that enable digital parental support to be used [B, C (*Interplay* intervention), and D]; (3) parents or professionals with severe visual impairment or other physical disorder that would prevent them from using the touch feature on mobile phones [B, C (*Interplay* intervention), and D]; and (4) single parents or parental couples in which only one of the parents agrees to participate (B and D).

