#### Statistical Analyses

Participant answers to the questionnaires will be transferred directly into the Statistical Package for the Social Sciences (SPSS), in which both descriptive and analytical analyses will be performed for comparisons and associations. Analyses will be controlled for such covariates as gender, age, education, marital status, length of parental couple relationship, and perceived economy. An alpha level of ≤ 0.05 will be accepted as significant. The prospective sample size is deemed to provide adequate statistical power for the analyses to be performed.

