Involving interdisciplinary professionals and consumers in early product design is critical in order to ensure that the final product is usable and acceptable, as well as that it will lead toward healthy behaviors (43). *Childbirth Journey* represents just that: a digital tool developed by multidisciplinary medical professionals with initial input from expectant mothers and partners. Furthermore, healthcare professionals should support the evaluation of existing parenting applications to ensure that parents are acquainted with the most effective and up-to-date options (44). Obtaining healthcare professional experiences of the digital tool in our study will ensure that *Childbirth Journey* is presented to professionals, but most importantly, their feedback on the tool will bring valuable material that, together with the parents' experiences, will be evaluated and utilized in finalizing the product. Beyond the experience obtained with *Childbirth Journey*, parents will have the possibility to use the other digital tool in our study, *Interplay*, which has the intention to enhance new parents' couple relationships and cooperation within parenthood. As mentioned, the two serious games that are to be explored for this study represent different characteristics; one is a story-driven educational serious game (*Childbirth Journey*) focussed on conveying information controlled by healthcare professionals, the other is a casual quiz focussed on interaction and communication between parental couples (*Interplay*). Because the two serious games represent both different characteristics and different stages of development, we will be able to access diverse views and gain a deeper understanding of how digital tools should be provided to expectant and new parents.

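### Study D enrols complete couples, but its sample size counts individual parents and its adjusted analyses make no allowance for dependence within couples

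*Protocol article*

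**What the plan says.** **Who enters.** In the Protocol article, Participants, the fourth exclusion criterion removes "single parents or parental couples in which only one of the parents agrees to participate (B and D"). Study D therefore consists of complete couples. The article gives no number of couples; 120 parents make 60.

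**How it is sized.** The same section says the calculation is "based on an expected relationship of 0.4, which requires at least 100 participants", "given power of 80% and significance level 0.05", and sets a target of about 120 parents. It does not say what kind of coefficient 0.4 is, and it gives no within-couple correlation or design effect.

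**What is measured.** Under Data Collection, each participant answers QDR36, SOC-13 and the social support scale at Q1 and again at Q2, six months later. QDR36 is described as covering five dimensions of the parents' dyad. The Discussion describes Interplay in these terms: "the other is a casual quiz focussed on interaction and communication between parental couples".

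**How it is analysed.** Statistical Analyses announces comparisons and associations in SPSS and adds: "Analyses will be controlled for such covariates as gender, age, education, marital status, length of parental couple relationship, and perceived economy". The threshold is given as "An alpha level of ≤ 0.05 will be accepted as significant". The sample size is then declared adequate for these analyses. The section names neither a unit of analysis nor any allowance for couples.

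**The concern.** Two partners who rate one relationship will usually give correlated scores, so 120 questionnaires from 60 couples do not carry the information of 120 unrelated parents. An individual-level regression that ignores this misstates its standard errors, and the direction depends on the predictor:

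- A predictor shared by the couple, such as relationship length, gets standard errors that are too small.
- A predictor that differs systematically between partners, usually gender, gets standard errors that are too large.

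The covariate list contains both kinds, so no single inflation factor repairs all coefficients. What is at stake is the validity of the p-values in Study D's associations, and whether the sample size statement means what it appears to mean.

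**Working it through.** **1. The plan's own figure.** Inputs from Participants: 0.4, 80% power, alpha 0.05 (two-sided assumed). Read as a correlation, with Fisher's z:

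n = ((1.960 + 0.842) / atanh(0.4))² + 3 = (2.802 / 0.4236)² + 3 = 46.7, so 47.

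A one-sided test gives 38. The stated 100 is not reproduced. Other readings come near 100 only with assumptions that the article does not state:

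- a correlation of 0.4 at 99% power: 106;
- an overall F test of a multiple correlation of 0.4: 79 with 6 predictors, 99 to 102 with 11 to 12;
- a paired difference of 0.4 SD: 50 to 51 pairs, which is 100 to 102 parents if the pair is the couple;
- two independent groups differing by 0.4 SD: 99 per group, although Study D has no groups.

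**2. Effect of couples on power.** For pairs, design effect DE = 1 + ICCx × ICCy, where x is the predictor and y the outcome. If the predictor is identical within couples, ICCx = 1 and DE = 1 + ICCy. Effective n = 120 / DE, and power for r = 0.4 is Φ(0.4236 × √(n − 3) − 1.960).

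| DE | Effective n | Power, r = 0.4 |
|---|---|---|
| 1.0 | 120 | 0.996 |
| 1.3 | 92.3 | 0.980 |
| 1.5 | 80 | 0.961 |
| 1.7 | 70.6 | 0.936 |
| 2.0 (worst case) | 60 | 0.892 |

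With only 50 complete couples (100 parents), the worst case is 0.828.

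If instead 100 is taken as the number of independent observations needed, 120 parents suffice only up to DE = 120/100 = 1.2. The requirement becomes 130, 150 and 200 parents at DE 1.3, 1.5 and 2.0.

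**3. Effect on type I error.** For an individual-level test with no couple term, the true error at nominal 5% is 2 × (1 − Φ(1.960 / √DE)). Simulation used 60 couples and 20,000 replicates. All ICCs are assumed.

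| Predictor ICC | Outcome ICC | DE | Formula | Simulated |
|---|---|---|---|---|
| 1 (couple-shared) | 0.3 | 1.30 | 8.6% | 8.5% |
| 1 | 0.5 | 1.50 | 11.0% | 11.2% |
| 1 | 0.7 | 1.70 | 13.3% | 13.2% |
| 0.5 | 0.5 | 1.25 | 8.0% | 7.8% |
| 0.3 | 0.3 | 1.09 | 6.1% | 6.0% |
| 0 | 0.5 | 1.00 | 5.0% | 5.0% |
| −1 (partner contrast) | 0.5 | 0.50 | 0.6% | 0.7% |

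**The case against.** **The article does not say parents are analysed as independent.** This stands. A reader might infer a fixed individual-level model, but Statistical Analyses names no model, and a random effect or clustered errors could be set out in an analysis plan that is not shown. Independence is inferred from the counting unit and from silence, so the error rates are conditional. What remains is that the article itself fixes couple-only entry, counts the sample in individuals and declares it adequate. A later plan would not by itself correct that count.

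**Power is not the problem.** This also stands. A reader might compare 120/1.3 = 92, 120/1.5 = 80 and 120/1.7 = 71 with the required 100 and conclude that Study D is underpowered. That accepts the 100 without checking it. For a correlation of 0.4 about 47 independent observations suffice, and 60 couples supply at least 60.

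**The largest error rates are the extreme case.** They assume a predictor identical within couples. The Objectives speak of individual sessions, and SOC-13 and perceived social support are individual measures, so it does not follow that usage is the same for both partners. For predictors only partly alike within couples, 6 to 8% is the fairer range. Relationship length, however, is shared by definition.

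**The study is exploratory and precedes a planned randomised trial.** True, and this lowers the stakes. It does not make an unprotected p-value valid against the significance threshold the article adopts.

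**Conclusion.** The point holds as a mismatch between couple-only recruitment and a sample size and analysis text that take no account of couples. If parents are analysed individually, the true level of a nominal 5% test runs from well below 5% (partner contrasts) through about 5% (predictors uncorrelated within couples) and 6 to 8% (both ICCs 0.3 to 0.5) to 8.6 to 13% (couple-shared predictors, outcome ICC 0.3 to 0.7). These figures rest on assumed ICCs and on 60 couples inferred from 120 parents.

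The documents do not support saying that the planned standard errors are certainly wrong, or that Study D lacks power for its stated effect. Power for a correlation of 0.4 stays at 89% or more at any ICC with 60 complete couples. That conclusion depends on reading 0.4 as a correlation, which the article leaves undefined. The separate defect in the power statement is that 100 does not follow from that input and carries no couple adjustment.

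**What to change.** - **Data Collection:** record a pseudonymous couple code at Q1 and Q2. It must be in place before Q1 goes out, because partners may not be linkable afterwards.
- **Statistical Analyses:** name the couple as the sampling unit, and fit the models with couple as a random effect or with couple-clustered standard errors.
- **Participants:** restate the sample size as about 60 couples, with a defined effect measure, an assumed ICC range and the resulting power. Correct or explain the figure of 100.
- **Optional:** split usage into a couple mean and a within-couple deviation. This is possible only if log data can be linked pseudonymously to person and couple. Data Collection says the logs will hold nothing that identifies individuals and will be studied only in aggregate, so the two must first be reconciled.

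The cost is one extra questionnaire field and some wording. No extra participants are needed for a correlation of 0.4. Intervals for couple-level predictors widen by √(1 + ICC), for example √1.3 = 1.14 at an outcome ICC of 0.3 and √1.7 = 1.30 at 0.7.
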